## Abstract

**Background:**

Craving associated with drug-related memory is one of the key factors that induce the relapse of methamphetamine (MA). Disruption or modulation of the reconsolidation of drug-related memory may serve as an option for clinical treatment of MA addiction. This protocol proposes to use virtual reality (VR) to retrieve drug-associated memory and then use transcranial magnetic stimulation (TMS) at the neural circuit that encodes the reward value of drug cues to provide a non-invasive intervention during reconsolidation. We aim to evaluate the effectiveness of TMS treatment after VR retrieval on the reduction of cue reactivity and craving of MA.

**Methods:**

This is a randomized, double-blind, sham-controlled, parallel group trial, targeting participants with MA use disorder aged from 18 to 45 years old. Forty-five eligible volunteers in Shanxi Drug Rehabilitation Center will be recruited and be randomly allocated into three parallel groups, receiving either 1) MA-related cues retrieval in VR combined with active TMS (MA VR scene + TBS) or 2) sham TMS (MA VR scene + sham TBS), or 3) neutral cues retrieval in VR combined with active TMS (neutral VR scene + TBS). Two sessions of post-VR-retrieval TBS will be scheduled on two separate days within 1 week. The primary outcome will detect the memory-related activity by the electroencephalography (EEG) reactivity to drug cues in VR scenes. Secondary outcomes are the self-reported MA craving in VR scene, the physiological parameter (cue-induced heart rate) and the scores of psychological questionnaires including anxiety, depression, and mood. All primary and secondary outcomes will be assessed at baseline, 1-week, and 1-month post-intervention. Assessments will be compared between the groups of 1) MA VR scene + TBS, 2) MA VR scene + sham TBS and 3) neutral VR scene + TBS.

**Discussion:**

This will be the first study to examine whether the TMS modulation after VR retrieval can reduce self-reported craving and drug-related cue reactivity. It will promote the understanding of the neural circuit mechanism of the reconsolidation-based intervention and provide an effective treatment for MA use disorder patients.

**Clinical Trial Registration:**

[Chinese Clinical Trial Registry], identifier [ChiCTR1900026902]. Registered on 26 October 2019.

## Introduction

Methamphetamine (MA) is a potent psychostimulant highly addictive for its euphoric and stimulant effects. It is the most prevalent drug of abuse in China accounting for more than 50% substance users. The number of MA users exceeds one million according to an official survey conducted in 2020 (1) while there is no established therapy for MA dependence (2). A core symptom of MA use disorder (MUD) is craving that lingers even after a long-term abstinence. Craving for MA positively correlates with the severity of MUD (3) and predicts relapse (4). Craving can be induced by cues and contexts associated with drug-related episodic memory (5). The vivid and multi-sensory episodic memory formed through repeated MA use persists after abstinence and drives craving (6), suggesting that intervention on drug-related episodic memory may reduce craving and contribute to relapse-prevention of MUD.

It has been postulated that long-term episodic memories could be modified during a time window called “reconsolidation” after memory retrieval (7, 8). Within the reconsolidation window, memories could be updated, strengthened, or weakened by manipulation of the electrophysiological or neurochemical activity within the neural network encoding the retrieved memory (7, 9). A feature of reconsolidation interventions is that a single or limited numbers of interventions can generate long-term effect for weeks or even months (10–14). Particularly, post-retrieval intervention during reconsolidation reduces the emotional or motivational value of reward cues embedded in episodic memories without disrupting the cognitive component of the cue-reward associative memory (15). Compared to a general reward cue, the motivational value, or incentive salience, of MA cues is stronger and more enduring. Thus, a major difficulty is how to reactivate and destabilize drug-related memory to make it more labile and susceptible to updating. We believe that virtual reality (VR) can reactivate MA-using memory because a vivid, immersive, and interactive virtual scenario carries more contextual information than pictures or videos, which can trigger re-experiencing reward-related memory and potent cravings (16–19). Therefore, we propose that the use of VR to retrieve memory and an MA-craving state provides the possibility for the subsequent intervention.

The reconsolidation of drug-related episodic memory recruits the medial prefrontal cortex and basolateral amygdala (BLA) circuit (20–22) where local pharmacological intervention during reconsolidation can degrade the emotional/motivational impact of the drug-related cues (15). The medial prefrontal cortex is a major cortical center involved in value computation and representation with its multiple sub-regions conducting varied functions (23, 24). The orbitofrontal cortex (OFC) is critical for encoding and updating the incentive value of reward cues in a state-based manner by a reciprocal connection with the BLA (25–27). Clinical studies in substance users found that the OFC dysfunction leads to impaired motives for general rewards but an increased motivation for addictive drugs which gradually develops into a pathological substance craving (28). In addition, inhibition of the OFC or disruption of the OFC-BLA connectivity reduces context- or cue-induced drug seeking (28–31). Although the current evidence supports an idea that the OFC intervention has an immediate effect on cue-induced craving, there is no report on whether inhibition of the OFC can produce a sustained effect to reduce drug-seeking.

Transcranial magnetic stimulation (TMS) is a non-invasive method to modulate neural activity on cerebral cortex by generating a magnetic field close to the scalp over the target brain region (32). TMS with different parameters and stimulation sites can induce long-term changes that facilitate or reduce the activity of neurons or circuits (33). It has been applied as a physical treatment to many neurological and mental disorders such as major depressive disorder (34), obsessive-compulsive disorder (35), and post-traumatic stress disorder (36). Studies with TMS intervention targeting the OFC are rare but their encouraging results show that self-reported cravings for alcohol (28), cocaine (28), or smoking (37) were reduced immediately after OFC or related prefrontal cortex stimulation. Notably, a study on TMS interventions for MA patients compared the effects of stimulation targeting the dorsolateral prefrontal cortex (DLPFC) or ventromedial prefrontal cortex (vmPFC) or both regions for 2 weeks and found that all three treatments reduced MA craving, but TMS over the vmPFC or both yielded a shorter respondence time and a more pronounced effect on sleep quality (38). Another study for alcohol users showed that 10 days of medial prefrontal cortex TBS reduced the connectivity between multiple brain regions in reaction to alcohol cues as well as alcohol drinking up to 3 months after TBS treatment (39). This encouraging report suggests that neuromodulation like TBS on the neural circuit mediating reactivity to addictive drug-cue may achieve a sustained inhibitory effect on drug using.

The purpose of this protocol is to design a set of clinical treatments to obtain a sustainable inhibitory effect on the craving for MA after a limited number of interventions. We propose that TMS stimulation of the OFC within the time window of MA-related episodic memory reconsolidation will produce a continuous reduction in craving elicited by MA-related cues or context. In specific, we will use theta-burst stimulation (TBS), a new pattern of TMS, to modulate the activity in the OFC because of its advantage for stronger effects with shorter duration compared to conventional repetitive TMS (40). We will choose continuous TBS (cTBS) due to its promised effect on depression of cortical excitability (22, 31, 33). It has been delivered to the medial prefrontal cortex to decrease reactivity to alcohol-related cues and reduce drinking behavior in a recent studies (39). And cTBS has been used to disrupt OFC network activities in previous studies (41). Since an effective activation of episodic memory is important in reconsolidation-based treatment (42, 43), a series of vivid and immersive VR scenes related to MA using will be present for memory retrieval and craving self-rating (43–45). In addition to self-report craving, the cue-related electroencephalogram (EEG) activity in the VR scene will be recorded as an indirect measure of the degree of memory retrieval and craving (43, 46, 47). Compared to neutral scenarios, the incentive salience of drug-related cues is stronger to draw drug user's attention (48, 49). Attention bias for drug-related cues is associated with subjective craving and tendency to approach drug-related cues (50, 51), indicated by abnormal EEG activities of prefrontal cortex. For example, two studies reported that MA users showed specific EEG features induced by MA-related scenes presented by VR, such as decreased gamma activity in OFC and right DLPFC (52) and reduced EEG power in delta, theta, and alpha bands (53) comparing to neutral scenario. In addition, processing alcohol- or smoking-related cues coincided with surged frontal beta-band activity in binge drinkers (54) or smoker (55); the increased beta-band activity in response to the drug-related cues is associated with enhanced attention and alertness. A recent study further showed that a higher level of synchronization of medial prefrontal cortex for the beta-band activity in 1–3 months abstinent MUD group, compared to groups with longer or shorter abstinence. Meanwhile, MA craving was higher in the 1–3 months abstinence group than other groups (56). This finding suggests that increased prefrontal beta activity may serve as a robust indicator of MA craving.

In summary, we design a randomized-controlled study of memory reconsolidation-based TBS intervention for people with MUD. It aims to investigate the short-term and long-term effects of TBS treatment on reducing cue-induced craving and updating memory-related EEG reactivity for MUD patients. Meanwhile, the physiological parameter such as cue-induced heart rate and possible co-variables such as emotional and mental state will be considered.

## Methods/Designs

### Study Design

This is a randomized, sham-controlled double-blind study. Participants will be randomly assigned by main investigator to three parallel groups using computer-generated random numbers with a 1:1:1 allocation ratio, either receive (1) MA-related cues retrieval in VR combined with active TMS (group A: MA VR scene + TBS) or (2) sham TMS (group B: MA VR scene + sham TBS), or (3) neutral cues retrieval in VR combined with active TMS (group C: neutral VR scene + TBS). Participants, outcome assessors, and data analysts will be blinded to the group assignment during treatment sessions. The doctors delivering TMS treatment will know the allocation sequence but will not be involved in the assessment. Once treatment is completed, participants will be asked to guess the specified intervention they have received to determine the actual effect of TBS. Then the clinical evaluator will debrief the participants about the study procedures. The two “VR retrieval–TBS” treatment sessions will be scheduled in 2 days within 1 week using an MA-related or neutral VR scene. Clinical, psychological questionnaires and EEG will be carried out at baseline (T0), each treatment session (T1/T2), the week of the last treatment (T3) and over 1 month after treatment (T4), as shown in Figures 1, 2. This protocol follows SPIRIT recommendations.

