### Participants

Participants with MUD in Shanxi Drug Rehabilitation Center will be voluntarily recruited to this treatment. After initial confirmation, eligible participants will then be required to sign an informed consent. The number and reasons of exclusion individuals, as well as those who reject or withdraw consent will also be recorded. *Inclusion criteria:* Selected participants will have to (1) be clinically diagnosed with Amphetamine-Type Substance Use Disorder according to Diagnostic and Statistical Manual of Mental Disorders (DSM-5) criteria, (2) abstinence periods at least 2 weeks without obvious withdrawal symptoms (e.g., drowsiness and dysphoria), (3) be aged 18 and 45 years old, and be right-handed, (4) be able to speak and read Chinese, (5) sign a consent form before intervention procedure.

*Non-inclusion criteria:* Participants meeting at least one of the following criteria will not be enrolled in this study: (1) meeting the diagnostic criteria of any other psychiatric disorder under DSM-5; (2) using other kinds of drugs (e.g., heroin, cocaine) in the past 30 days; (3) having contraindications to TMS treatment (head trauma, epilepsy or the history of epilepsy, metal implant, pregnancy and so on); (4) having a history of mental illness or a family history of mental illness; (5) be insensitive to VR scene (identified at the baseline); (6) having received psycho-therapy or TMS intervention in the last 6 months; (7) receiving medication treatment recently; (8) illiteracy; (9) having visual or hearing problems; (10) the individual threshold of TMS was higher than 50% of the maximum output of the TMS equipment; (11) scheduled to receive psycho-therapy or medication treatment for the next 2 months. *Exit criteria:* Participants will be allowed to withdraw from the clinical trial if they (1) voluntarily wish to stop the TBS sessions; (2) can hardly tolerate any aversive reactions (e.g., itching, numbing) or have a desire for other treatments; (3) do not complete the TBS sessions for other reasons; (4) suffer from worsening symptoms such as enhanced craving.

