## Ethics Statement

The Ethics Committee of the Institute of Psychology, Chinese Academy of Sciences has approved this protocol (H19007). The study will be carried out in accordance with the recommendations of this committee. All participants will sign an informed consent form (which will be gathered by the main investigator), providing their wish to do so, in accordance with the Declaration of Helsinki and with national and local regulations. The study is registered in the Chinese Clinical Trial Registry (www.chictr.org.cn) with ID: ChiCTR1900026902.

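### One role both takes consent and assigns the arm, and the treating doctors know the allocation sequence, so the stated arrangement does not protect allocation concealment

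*Protocol article*

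**What the plan says.** Study Design fixes who assigns: "Participants will be randomly assigned by main investigator to three parallel groups using computer-generated random numbers with a 1:1:1 allocation ratio". The Ethics Statement says who handles consent: "All participants will sign an informed consent form (which will be gathered by the main investigator". Under Participants, consent comes after eligibility has first been confirmed and is required for entry: "After initial confirmation, eligible participants will then be required to sign an informed consent".

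Study Design also states who is blinded: "Participants, outcome assessors, and data analysts will be blinded to the group assignment during treatment sessions". The main investigator, the screener and the treating doctors are not on that list. For the doctors it says: "The doctors delivering TMS treatment will know the allocation sequence but will not be involved in the assessment".

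Three other places bear on entry:

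- Data Collection and Statistical Methods gives the eligibility check to a screener, before randomisation.
- The non-inclusion criteria include one that needs a TMS measurement: "the individual threshold of TMS was higher than 50% of the maximum output of the TMS equipment". Under Intensity Identification a TMS provider finds the site, and threshold is defined by finger movement in at least 5 of 10 consecutive trials.
- Under Monitoring, Identification Method and Management System, the criteria are confirmed a second time before stimulation is given.

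**The concern.** Randomisation protects the A versus B and A versus C contrasts only if nobody who can influence entry can foresee the next assignment. Here one role both completes entry, through consent, and makes the assignment. A second group knows the sequence and is kept away only from outcome assessment.

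If the next arm can be known before entry is settled, a candidate can be deferred, encouraged or judged ineligible with that arm in mind. Some criteria leave room for this. Insensitivity to the VR scene and recent medication carry no cut-off in the article. The first of these is also close to the cue reactivity that the trial measures. Blinded assessors and analysts cannot undo selection that took place before treatment, and 15 participants per arm leave little room to absorb it.

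**Working it through.** The point rests on none of the plan's calculations. The check is mainly a comparison of the stated roles.

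**Roles side by side**

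| Step | Who, as stated | Separated from the sequence? |
|---|---|---|
| Eligibility check before randomisation | Screener | Not stated |
| Gathering consent | Main investigator | No: the same role assigns |
| Assignment | Main investigator | Not applicable |
| Motor threshold (an entry criterion) | TMS provider | Not stated; not said to be a treating doctor |
| Second check before stimulation | Not named | The treating doctor knows the arm by then |
| Treatment | Doctors delivering TMS | No: they know the sequence |
| Outcome assessment | Assessors | Yes: blinded, and the treating doctors take no part |

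The only barrier placed around the people who know the sequence is at assessment. None is stated at consent, screening or threshold measurement. This follows from what the article says about roles. It does not depend on the article's silence about envelopes or a central service.

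**Illustration of size, under assumed behaviour**

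The only input from the protocol is 15 per group (45 in three arms). Everything else is assumed.

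*Deferral when arm A is next.* Suppose the worst-prognosis share q of candidates is turned away whenever the next slot is arm A, and prognosis is standard normal. The arm A mean shifts by φ(z)/(1 − q), where z cuts off the upper tail q:

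- q = 5%: 0.1031/0.95 = 0.109 SD
- q = 10%: 0.1755/0.90 = 0.195 SD
- q = 20%: 0.2800/0.80 = 0.350 SD

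For scale, a two-sided 5% t-test of 15 versus 15 has 80% power for a difference of about 1.06 SD. The shifts are therefore about 10%, 18% and 33% of that difference (0.109/1.06, 0.195/1.06, 0.350/1.06).

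*Steering both ways.* A simulation of 4,000 trials per setting had no true effect. A share q of entries was steered: favourable candidates when arm A was next, unfavourable ones otherwise. The score was taken as the outcome itself.

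| q | A − B shift (SD) | Type I error, next arm known | Type I error, concealed |
|---|---|---|---|
| 0% | 0.01 | 0.053 | 0.057 |
| 10% | −0.15 | 0.075 | 0.054 |
| 20% | −0.32 | 0.138 | 0.053 |
| 30% | −0.47 | 0.259 | 0.050 |
| 50% | −0.79 | 0.622 | 0.053 |

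With concealment, the same wish to steer leaves the error near 5%.

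**The case against.** The strongest reply is that the article names a screener who settles eligibility before randomisation, so neither the main investigator nor the treating doctors are shown deciding who enters. This counts against saying that upcoming assignments are visible to the people who decide entry. A reader might infer that, but the text does not state it. The investigator's part in entry is explicit only through consent, and nothing says that the investigator sees a list in advance. Computer-generated numbers could be drawn one at a time after entry. The reply does not remove the problem, because the screener is not said to be separate from these roles or unaware of the sequence.

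Second, the sentence about the doctors stands among the blinding statements and may mean only that treaters know each participant's arm. That is hard to avoid, since the sham coil carries an extra sheath (Sham TBS Protocol). This reading is possible. Literally, though, a sequence includes assignments still to come, and treaters need only the current one.

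Third, a reader might infer that the treating doctors can tilt the motor-threshold criterion. No section says that the TMS provider is a treating doctor, the reading follows a 5-of-10 rule against a numeric cut-off, and nothing links threshold to prognosis. That inference should not be pressed.

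Fourth, the full protocol may contain a concealment step, and an article may leave it out. That is fair, so the point does not rest on the missing method. A concealment step elsewhere would still have to be squared with doctors who know the sequence.

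Finally, the illustration assumes that the whole prognostic shift reaches the outcome. The planned comparison is baseline against post-test, so a stable difference between arms would largely cancel. Only selection on something that predicts change would carry through.

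**Conclusion.** The point holds in a limited form. Consent and assignment rest with one role, and the treating doctors know the sequence and are separated only from assessment. The screener's independence is not stated, and the second check of the criteria comes when the treating doctor knows the arm. Allocation concealment is therefore unprotected as written, and selection bias is possible.

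The documents do not show that anyone has seen or used upcoming assignments, or that the full protocol has no concealment step. They also give no size for the bias. The figures above depend wholly on assumed behaviour and on an outcome that carries the full prognostic shift. They do not support saying that a few steered entries would decide the result: steering 10% of entries raises the error only to about 0.08, and less would be expected for change from baseline. The arrangement should be changed because the threat is to randomisation itself and the remedy is cheap. It does not by itself invalidate the trial.

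**What to change.** 1. Have an existing team member who does not consent, screen, treat or assess generate and hold the list. Use simple randomisation, or blocks of varying and undisclosed size. Fixed blocks would be a poor choice, because with unblinded treaters at one site the last assignments in a block could be worked out.
2. Release each assignment, for example by sequentially numbered opaque sealed envelope, only after consent, T0, the VR-sensitivity check and the motor-threshold check are recorded.
3. In Study Design, replace the statement that the doctors know the sequence with: *will learn each participant's assignment only at that participant's first treatment session*.
4. State that the screener has no access to the list.
5. Analyse everyone randomised in the assigned group, whatever the later check of the criteria finds, so that this check cannot select participants after assignment.

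The cost is protocol wording, a set of envelopes and minor logistics. The sample size, visits and treatment do not change. The one condition is that a team member free of those four roles can be named.

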
All VR scenes will be displayed by HTC VIVE VR system containing a wired headset (110 degrees, 1,080 × 1,200, 90 Hz) and a wireless handle controller to provide participants with direct, realistic interactions. With a head-mounted display, participants wearing a headset will immerse into the VR scenes. The wireless controller will also be accessible for participants to interact with objects in the VR scenes and rate VAS. The VR scenes will be monitored by a care provider on a desk computer (Alienware 15-R2748, i7-7700HQ 16G 256GSSD+1T GTX1070 8G discrete graphics FHD). These VR scenes have been developed by our collaborative team with unity 3D and used in our previous study (43).

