#### TBS Protocol

##### Target to Stimulate

Refer to related research and large-scale Magnetic Resonance Imaging/functional Magnetic Resonance Imaging (MRI/fMRI) data from https://neurosynth.org/, the OFC, functioning (including both orbital and media area) with encoding specific stimuli value (59, 60) has been located with an averaged MNI coordinates (-4, 36,−18). Following previous suggestion (61), the stimulated site targeting OFC will be located according to the standardized international EEG 10–20 position (Fp1). This brain area will be labeled on an EEG 10 - 20 system cap. The coil will be placed tangent to the scalp at the contact point (Figure 3). During the TBS or sham treatment, the TMS coil over Fp1 will be fixed by a holder on the coil's handle during the treatment. We will pause to adjust the position if there is any movement of the coil or head according to the participant's feedback.

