##### TBS Pattern

The cTBS will be applied to reduce activation of the OFC circuit. TBS sessions will be carried out with a hand-held figure-of-eight coil with the size of 90 mm diameter of one half of the “8” shape (B9076, Yiruide Co., Wuhan, China), attached to a YRD CCY-I stimulator (Yiruide Co., Wuhan, China). Following a 10-min rest after memory retrieval, participants either in the MA VR scene + TBS group (*n* = 15) or in the MA VR scene + sham TBS group (*n* = 15) or in the neutral VR scene + TBS group (*n* = 15) will receive two TBS sessions within 1 week. In each session, all participants will receive two 1,800-pulse trains of cTBS in 5 min (three pulses are given at 50 Hz as one burst; a burst will be given every 200 s as 5 Hz; one train for 120s, containing 1,800 pulses) with a pulse intensity of 80% of RMT following Hanlon et al. (62)'s suggestion. A 60-s break will give to participants after the first train (1,800 pulses). The choice of TBS intensity will consider the participants' real-time feedback and health condition to TMS stimuli. If a participant reported unbearable discomfort with TBS stimulation, we will turn down the intensity gradually until acceptable. If a participant still reported unbearable discomfort when the stimulation intensity was lower than 60% of the RMT, this participant will withdraw from the experiment. These parameters have been applied by previous studies (62) and proposed in safety guidelines (63).

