#### Identification Method and Management System

(1) above potential risks will be considered within exclusion criteria to select adequate participants at the screening stage. These criteria will be re-confirmed again before the delivery of stimulation;

(2) individualized parameters for treatment: the intensity will be identified as RMT according to the individual threshold, and it will be adjusted (80–110% RMT) based on the tolerance of each patient;

(3) if there is persistent pain, intolerable, or the participant subjectively requests to withdraw, the treatment shall not be continued and concomitant care will be offered.

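### The doctors delivering TMS are told the full three-arm allocation although they need only the coil type, which leaves an avoidable risk of performance bias in the retrieval contrast (group A against group C)

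*Protocol article*

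**What the plan says.** Study Design lists who is blinded: "Participants, outcome assessors, and data analysts will be blinded to the group assignment during treatment sessions". The operators are not on that list, and the next sentence deals with them directly: "The doctors delivering TMS treatment will know the allocation sequence but will not be involved in the assessment".

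The same section defines the two arms that matter here. Group A is "MA-related cues retrieval in VR combined with active TMS (group A: MA VR scene + TBS" and group C is "neutral cues retrieval in VR combined with active TMS (group C: neutral VR scene + TBS". The stimulation is the same and the scene differs. Only group B uses another device, a sham coil with an additional black sheath (Sham TBS Protocol).

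Three places allow delivery to vary during a session:

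- **TBS Pattern:** the planned intensity is 80% of resting motor threshold (RMT). On unbearable discomfort, "we will turn down the intensity gradually until acceptable", with withdrawal if discomfort persists below 60% RMT.
- **Identification Method and Management System:** "it will be adjusted (80–110% RMT) based on the tolerance of each patient".
- **Target to Stimulate:** a holder fixes the coil, but "We will pause to adjust the position if there is any movement of the coil or head", according to the participant's feedback.

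On the scene itself, VR Retrieval says: "The VR scenes will be monitored by a care provider on a desk computer". No section gives a reason for telling the TMS doctors which scene a participant saw.

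**The concern.** A against B compares active with sham stimulation after the same scene. A against C compares the same stimulation after different scenes. A against C is therefore the contrast that tests the trial's central idea, that stimulation works because it follows retrieval of drug memory.

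With the sheathed sham coil, operator knowledge of active or sham cannot be avoided. Knowledge of A or C can be limited, because the treatment given at the coil is identical. By disclosing the whole sequence, the plan gives up a protection in the one contrast where it is available.

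If operators who know the scene handle A and C differently, for example by reducing intensity sooner or repositioning more readily in one group, the delivered stimulation would differ between the groups. Blinded assessors would record the resulting outcome difference faithfully, and it would be read as an effect of retrieval. Excluding the operators from assessment guards against detection bias, but not against performance bias during treatment.

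**Working it through.** The plan gives no figure for this point, so the main check sets the sections side by side.

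**1. What the operator needs to know.**

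| Group | Scene before stimulation | Coil |
|---|---|---|
| A | methamphetamine | active |
| B | methamphetamine | sham |
| C | neutral | active |

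The coil column takes two values and the allocation takes three. Active or sham is enough to deliver treatment correctly. The extra information in the sequence, for a participant on the active coil, is exactly A or C.

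**2. Whether the steps can be separated.** Intervention and TBS Pattern put a 10-minute interval between scene and stimulation. VR Retrieval assigns monitoring of the scene to a care provider, while Study Design speaks of doctors delivering TMS. The different terms suggest different people, but no section says so.

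**3. Whether delivery can vary.** Intensity and coil position can both change during treatment (TBS Pattern, Identification Method and Management System, Target to Stimulate). In each case the trigger is the participant's discomfort, tolerance or feedback. These sentences use the first person plural or the passive, so attributing the steps to the TMS doctors is an inference, though the natural one.

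**4. Illustration of sensitivity.** Inputs: 15 per group (TBS Pattern), two-tailed alpha 0.05 (Primary Outcome Measure), and an assumed spurious A–C shift of d standard deviations with no true retrieval effect. For a two-sample t-test:

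- degrees of freedom = 15 + 15 − 2 = 28, critical value 2.048;
- noncentrality = d × √(15/2) = 2.739 × d;
- rejection probability = P(|T| > 2.048), with T noncentral t on 28 degrees of freedom.

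| Assumed shift d (SD) | Noncentrality | Rejection probability |
|---|---|---|
| 0 | 0 | 0.050 |
| 0.1 | 0.274 | 0.058 |
| 0.2 | 0.548 | 0.083 |
| 0.3 | 0.822 | 0.125 |
| 0.4 | 1.095 | 0.185 |

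The values of d are assumptions. Nothing in the protocol links operator knowledge to a shift of any size. The test is also a simplification: Inferential Statistics names paired t-tests and a three-group repeated-measures ANOVA. The same table would apply to any source of bias at this sample size.

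**The case against.** The case on the other side has several parts, and much of it stands.

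- **Staffing.** The protocol does not say that the VR care provider and the TMS doctor are different people. A session lasts 30 to 40 minutes including preparation, and one operator could run all of it. A reader might infer that masking costs nothing. The text does not support that unconditionally.
- **Full blinding.** A reader might infer that the operator could be fully blinded for A against C. That goes too far. The participant has just seen the scene and then gives the operator feedback, so the scene may be disclosed in conversation.
- **Operator latitude.** A reader might join the 60% in TBS Pattern to the 110% in Identification Method and Management System and conclude that operators may choose anywhere in between. The two sections give differing ranges, which is a separate matter to reconcile. They do not describe free choice across the span, and the adjustments are prompted by the participant. The coil holder narrows the room for differences further.
- **Outcome protection.** The primary outcome is EEG band power computed in the device, with the post-test 1 to 4 days after the last session, and assessors and analysts are blinded. This limits the effect of operator expectation. It does not stop a real difference in delivered stimulation from reaching the outcome, and the self-rated craving scale is less protected.
- **Double-blind label.** A reader might infer that the label is false. It is not contradicted, because participants and assessors are blinded and the operators' knowledge is openly stated.
- **Condensed article.** Split code lists and session logs are operational detail that an article may leave to the full protocol. The point, however, rests on a rule that the article states, not on something it omits.

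These arguments limit the size of the bias and the certainty of the remedy. None gives a reason for telling the operator A from C.

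**Conclusion.** The point holds in a limited form. The stated rule gives the operators more of the allocation than they need, and the surplus is the distinction between the two arms that isolate retrieval. This creates an avoidable risk of performance bias in A against C, through intensity changes and repositioning that participants prompt and operators carry out.

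The size of any bias is unknown. The rejection probabilities of 5.8% to 18.5% for assumed shifts of 0.1 to 0.4 SD show sensitivity at 15 per group and do not estimate this trial's error rate.

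The conclusion rests on two readings. The first is that knowing the allocation sequence means knowing all three arms, which is the plain sense of the sentence. The second is that the people delivering TMS make the adjustments, which is inferred.

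**What to change.** Replace the Study Design sentence on the TMS doctors with wording to this effect:

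- The TMS doctor receives only the coil code (active or sham) for the participant being treated, is not told the scene and does not attend the VR session.
- The care provider who monitors the scene receives only the scene code.
- Participants are asked not to discuss the scene with the operator.
- Delivered intensity (% RMT), pauses and repositioning are logged at each session and tabulated for A against C.

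The cost is a split allocation list and a short log. No extra staff are needed if, as the wording suggests, the care provider and the TMS doctor are different people. If one person does both, separating the roles is a staffing cost. Even without that separation, the log and the A-against-C table still apply and would show whether delivery differed. The split must be in place before treatment starts, because no later analysis can restore the masking.

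This change leaves the intensity rules as they are. The differing intensity ranges in TBS Pattern and in Identification Method and Management System must be reconciled separately.
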